**Fig. 3 Fig3:**
[figure not shown]
Resistance training and balance training

### Criteria for discontinuing or modifying allocated interventions {11b}

A participant can opt out of the study at any time point. Treatment will be halted immediately, and required treatment will be provided whenever there is an adverse reaction, including pain, swelling, and discomfort. Consultations with the orthopedic surgeons will be made available via the research clinic from the Department of Orthopaedics and Traumatology, CUHK.

### Strategies to improve adherence to interventions {11c}

The opening hours of the Sports Performance and Biomechanics Laboratory will be extended to evening hours for the convenience of participants and to facilitate their participation. In addition, participants will be asked if there is any difficulty with the exercise regime whenever they come for the PEMF therapy.

### Relevant concomitant care permitted or prohibited during the trial {11d}

Participants are allowed to participate in their usual activities; no restrictions or changes to their daily activities will be required.

### Provisions for post-trial care {30}

Participants will have access to the research clinic from the Department of Orthopaedics and Traumatology, CUHK, if they experience any adverse reaction.

### Outcomes {12}

#### Primary outcome

Single leg standing test will be assessed on the TekScan MatScan® pressure mat model 3150 (TekScan Inc, South Boston, USA) to evaluate the postural control stability. The TekScan MatScan® is a low-profile floor mat (5 mm thick) and consists of 2288 resistive sensors (1.4 sensors/cm^2^) with a sampling frequency of 40 Hz and has been well-validated in other populations [32]. The mat will provide measures of anterior–posterior and mediolateral sway parameters described as the area and direction of the sway, distance and the direction traveled by the center of pressure (COP), and the variability of the distance traveled by COP. The Sway Analysis Module (SAM™) software will be used to analyze the sway data as seen in Fig. 4.

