**Fig. 4 Fig4:**
[figure not shown]
A TekScan result for anterior–posterior and mediolateral direction

On the pressure mat, participants will perform one practice trial and two trials of single limb stance on each leg with eyes opened and closed for 20 s, respectively. Participants will be required to stand on one leg unassisted (barefooted) and hands on the hips. This will be repeated for the non-affected leg as well. Before the commencement of the study, the assessor will undergo training, and the same assessor will oversee the experiment.

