##### The elasticity of the peroneal muscle

In addition, the shear elastic modulus of a muscle will be measured using ultrasonic shear wave elastography (Aixplorer, Supersonic Imagine, France) with a linear array probe. The region of interest (ROI) will be set near the center of each muscle. The analysis area will be a 5-mm diameter circle at the center of ROI. The shear elastic modulus will be measured three times per muscle, and the average of the three measured values will be used for further analysis. The shear elastic moduli of the PL and PB will be measured at proximal 25% from the head of the fibula to the lateral malleolus. For each Q-box, the maximum, minimum, and mean (in kPa) of the stiffness of the muscle are measured [41].

Other patient-reported outcome measures (PROM) will be employed to assess overall health and foot and ankle-related symptoms, pain, physical activity level, and health-related quality of life. Foot and Ankle Ability Measure (FAAM) will be used to assess the foot and ankle functional limitations among CAI individuals. The FAAM consists of 29 items, scored between 0 and 4, divided into two subscales: activities of daily living (21 items) and sports (8 items) [42]. For score analysis, the percentage of each subscale is used separately. According to the International Ankle Consortium, values of the day living activities < 90% and < 80% of the sports subscales of the FAAM score were considered unsatisfactory. Manchester-Oxford foot and ankle questionnaire (MOXFQ) is a 16-question self-reported score designed to evaluate the impact of foot and ankle problems on a person’s quality of life. The dimensions comprise 3 subscales: walking/standing problem (7 items), foot pain (5 items), and issues related to social interaction (4 items). After that, all three domains of the MOXFQ can be summed up and converted to a metric from 0 to 100 to create a summary index score (MOFXQ index) [43]. The pain score will be evaluated using the visual analog scale (VAS) ranging from 0 to 100. For the pain score, the higher the score indicates, the more severe the pain. The Short Form-36 questionnaires (SF-36) will be used to evaluate the health-related quality of life [44]. The International Physical Activity Questionnaire will be used to evaluate the physical activity levels [45]. All primary and secondary outcomes will be evaluated at baseline, 4th week, 8th week, 3rd month, 6th month, and 12th month follow-up.

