### Sample size {14}

Using the G*Power software (Germany) [46], a sample size of 48 (*n* = 24 per group, 1:1 allocation) is calculated based on the highest attrition rate of 40% at 3rd month follow-up of the study to retain a sample size of *n* = 28, according to similar research [47]. The calculation is according to the *F* test-repeated measures ANOVA, between factors, with an effect size of 0.3, an alpha level of 0.05, (1 − *β* err prob) = 0.8 to detect a significant change of the area of COP from 42.0 (± 23.6) to 25.4 (± 8.2) [48].

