### Statistical methods

#### Statistical methods for primary and secondary outcomes {20a}

SPSS version 26.0 will be used to analyze the primary and secondary outcomes based on the intention to treat (ITT) principle. ITT analysis will be performed using all randomized patients, including data for those terminated or lost to follow-up. During the process, assumptions will be checked, and remedial measures will be employed. The normality of the data will first be determined using the Kolmogorov–Smirnov test or the Shapiro–Wilk test (*p* > 0.05) to test for the normality of the data distribution. Other graphical methods such as Q-Q plots or histograms will also be used for visual inspection of the distribution and to assess the normality. If skewness and heteroscedasticity are present, transformation methodology such as Logarithm may be applied to make the distribution more symmetric and stabilize the variance. Baseline data and clinical variables between both groups will be compared using independent Student’s* t*-tests (parametric)/Mann–Whitney *U* test (non-parametric) for continuous data and the χ^2^ of independence for categorical data, respectively. Descriptive statistics will be presented in either mean (SD) or frequency (%). Thereafter, a repeated measure analysis of variance (RMANOVA) will be used to measure the time/exposure effects of muscle strength, Y balance test, LSDT, SLT, DROM, and results of the questionnaire between baseline, week 4, week 8, 3rd month, 6th month, and 1-year follow-up. Analysis of covariance (ANCOVA) will be conducted for baseline characteristics and prognostic factors as covariates and compared for group differences in different time points. Repeated-measure ANOVA and ANCOVA will be applied for all participants who have completed the assessments post-treatment. Bonferroni correction will be performed for multiple comparisons. Sensitivity analysis will be conducted by comparing the results of the imputation method to complete-case and available data analyses. The significant level will be set at 0.05.

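### The primary outcome names no deciding sway measure, eye condition, visit or test, while the sample size assumes a single test of COP area at an unsplit 0.05

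*Protocol article*

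**What the plan says.** **Outcomes {12}, Primary outcome.** The section names an assessment: "Single leg standing test will be assessed on the TekScan MatScan® pressure mat model 3150". The mat yields anterior–posterior and mediolateral outputs "described as the area and direction of the sway, distance and the direction traveled by the center of pressure (COP), and the variability" (the last referring to distance). None is singled out. Participants perform "two trials of single limb stance on each leg with eyes opened and closed for 20 s, respectively", and "This will be repeated for the non-affected leg as well". No rule is given for combining the two recorded trials.

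**Timing.** The end of the Outcomes section states: "All primary and secondary outcomes will be evaluated at baseline, 4th week, 8th week, 3rd month, 6th month, and 12th month follow-up". That is five post-baseline visits, and neither this section nor Trial design {8} calls one of them primary.

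**Statistical methods {20a}.** A repeated-measures ANOVA (RM-ANOVA) covers all six time points. ANCOVA is also planned for group differences at different time points. Neither is named as deciding. The significance level is 0.05, and "Bonferroni correction will be performed for multiple comparisons", with no family listed.

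**Sample size {14}.** The calculation is for an RM-ANOVA, between factors, "with an effect size of 0.3, an alpha level of 0.05" and power 0.8, "to detect a significant change of the area of COP". It retains 28 participants out of 48 randomised. Eye condition, leg, visit, number of measurements and correlation between measurements are not given.

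**The concern.** The outcome, sample size and analysis sections do not describe the same decision. The sample size assumes one test of one variable. The outcome section offers several variables under two eye conditions, and the analysis section can test them jointly over visits or visit by visit.

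The Bonferroni sentence does not settle this. If it covers the primary family, each test runs below 0.05 and the stated 80% power was computed at the wrong level. If it covers only other comparisons, the chance of at least one false positive primary finding exceeds 5%. On either reading one of the two stated figures fails.

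Timing adds to the risk. Under Implementation {16c} the allocation is revealed to the research team at the end of the intervention, while follow-up runs to 12 months. Under Data management {19} a member of that team analyses the data. A choice left open could therefore be made with the allocation known.

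**Working it through.** **Inputs from the protocol.** Effect size f = 0.3, alpha 0.05, power 0.80, two groups, 28 retained of 48 at 40% attrition (Sample size {14}); two eye conditions and at least three kinds of sway measure, namely area, distance and variability of distance (Primary outcome); six assessment times.

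**Assumptions.** m = 6 measurements, and a common correlation rho between them. Neither is stated in the protocol.

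**1. The plan's own figure.** Attrition step: 28 / (1 − 0.40) = 46.7, so 47, or 48 for equal arms. This reproduces.

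The 28 itself depends on the unstated inputs. For the between-factors test, lambda = f² × N × m / (1 + (m − 1) × rho), with 1 and N − 2 degrees of freedom. With m = 6, the N needed for 80% power is 24, 28, 32, 40 and 54 at rho = 0.1, 0.15, 0.2, 0.3 and 0.5. I take rho = 0.15 because it returns the stated 28, and show rho = 0.5 as a contrast.

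- rho = 0.15: lambda = 0.09 × 28 × 6 / 1.75 = 8.64; power 81% at 0.05.
- rho = 0.5: lambda = 0.09 × 28 × 6 / 3.5 = 4.32; power 52% at 0.05.

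**2. How many deciding tests (K).** This test pools over visits, so visits must not be counted again. On the affected leg:

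- COP area only, two eye conditions: K = 2.
- Area, distance and variability, two eye conditions: K = 3 × 2 = 6.
- If the visit-wise ANCOVAs count as well, COP area alone already gives 2 × 5 = 10.

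**3. Familywise error if each test is at 0.05.** Independent tests: 1 − 0.95^K. Correlated tests: simulation of equicorrelated normal statistics.

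| K | Independent | r = 0.5 | r = 0.8 |
|---|---|---|---|
| 2 | 9.8% | 9.1% | 7.8% |
| 6 | 26.5% | 21% | 14% |
| 10 | 40.1% | 29% | 17% |

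Sway measures from one recording are correlated, so the independent column is an upper value.

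**4. Power per test if Bonferroni covers the family** (alpha 0.05 / K, N = 28, m = 6, pooled test):

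| K | alpha | rho = 0.15 | rho = 0.5 |
|---|---|---|---|
| 1 | 0.05 | 81% | 52% |
| 2 | 0.025 | 71% | 40% |
| 6 | 0.0083 | 54% | 24% |

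At rho = 0.15, restoring 80% power for K = 2 needs 34 completers, and 34 / 0.6 = 56.7, so 57 randomised, or 58 for equal arms.

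**5. A single-visit test is not the test that was sized.** For a baseline-adjusted comparison at one visit, lambda = f² × N / (1 − r²), where r is the correlation with baseline. With f = 0.3:

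| N | r = 0 | r = 0.5 | r = 0.7 |
|---|---|---|---|
| 28 | 33% | 42% | 57% |
| 48 | 53% | 65% | 81% |

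**The case against.** **COP area is signalled as the key variable.** The sample size uses it, and the Discussion describes the single-leg-stance deficit as an increased COP area. The outcome section can be read as listing what the device reports, without declaring co-primary endpoints. This is fair, and it is why the smallest count above is K = 2. The protocol still does not call COP area primary, and eye condition, visit and test remain open on this reading.

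**Visits need not multiply the tests.** One RM-ANOVA group effect handles them jointly. A reader might multiply measures, eye conditions and five visits to 30 tests, and divide the alpha of the sized test by 30. The documents do not support that step: the sized test is pooled over visits, so its alpha cannot also be split by visit. Only the separate ANCOVAs bring visits into the count.

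**The other leg.** Treatment goes to the affected foot, and bilateral cases contribute one ankle, so counting both legs as primary would overstate the family. The counts above use the affected leg only.

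**Bonferroni is promised.** A reader might infer that any nominally significant sway measure may be declared the primary result. That goes too far. What the text supports is that the corrected family is undefined.

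**Twenty-eight is the planned floor.** Intention to treat with multiple imputation is also planned, so more data may contribute. But 28 is the number for which the protocol states 80% power.

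**Some of this belongs in an analysis plan.** Test hierarchy and the correction family often do, and I give those less weight. The primary variable, condition and time point belong in the outcome section.

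**Conclusion.** The point holds. As written, the primary outcome is a set of sway measures under two eye conditions with no deciding measure, condition, visit or test, and it does not match a sample size built on one COP-area test at 0.05.

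On the most favourable reading (K = 2) the size is moderate: familywise error of about 8–10%, or a loss of about 10 percentage points of power. With three measures (K = 6) it is about 14–26%, or power of 54%. Visit-wise ANCOVAs raise the count further.

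The power figures rest on m = 6 and rho = 0.15. The latter was chosen to match the stated 28 and is not taken from the document. At rho = 0.5 the single-test power is already 52%, which is a separate question about the sample size; Bonferroni then takes it to 40% (K = 2) or 24% (K = 6). The direction of the conclusion does not depend on rho.

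**What to change.** Before any unblinding, name one primary endpoint in the outcome section:

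- COP area, the measure already used for sizing, on the affected leg.
- One named eye condition.
- A stated rule for combining the two trials.
- One deciding between-group test at two-sided 0.05: either the RM-ANOVA group effect that was sized, or a baseline-adjusted comparison at one named visit. The choice of test and visit is the sponsor's.

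Make the other sway measures, the other eye condition, the contralateral leg and the other visits secondary. Confine Bonferroni or Holm to that listed family.

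Restate the power for the test chosen, with the number of measurements and the correlation assumed. Keeping the RM-ANOVA group effect adds no multiplicity penalty to the planned 48. Moving to a single visit requires a new calculation.

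**Cost.** Protocol wording and one recalculation, with no extra visits or measurements. The sponsor gives up claims of primary success on other sway measures and may have to state a power below 80%, or recruit more.

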**Fig. 4 Fig4:**
[figure not shown]
A TekScan result for anterior–posterior and mediolateral direction

On the pressure mat, participants will perform one practice trial and two trials of single limb stance on each leg with eyes opened and closed for 20 s, respectively. Participants will be required to stand on one leg unassisted (barefooted) and hands on the hips. This will be repeated for the non-affected leg as well. Before the commencement of the study, the assessor will undergo training, and the same assessor will oversee the experiment.

#### Secondary outcomes

##### Functional score

Cumberland Ankle Instability Tool (CAIT) score is a valid and reliable 9-item instrument used to identify self-perceived ankle instability. The instrument is scored on a 0 (worst) to 30 (best) scale, where a cut-off point of ≤ 24 denotes the presence of instability [33].

##### Dynamic balance

The Y balance test (YBT) evaluates the dynamic balance control in the CAI population. This test requires the integration of sensory inputs from visual, vestibular, and somatosensory pathways resulting in controlled motor outputs that recruit specific motor inputs. Participants must maintain unilateral stance, with their hands on the hips, balance on the involved limb, and reach with the uninvolved limb in the anterior, posteromedial, and posterolateral directions as far as possible [34]. The trial will not be counted and repeated if the participants lift their heels, fail to maintain their balance, remove their hands from their hips, or return to the starting point. Participants will complete 4 times of the trial and 3 analysis trials in each direction of the limb. The maximum distance in each direction, mainly, anterior, posteromedial, and posterolateral will be taken and divided by the limb length (LL) and multiplied by 100 [35]. LL will be measured using a flexible measuring tape from the anterior superior iliac spine to the medial ankle. The YBT composite (%) is calculated by the sum of three reach directions divided by 3 times the LL multiplied by 100.

##### Eversion muscle strength

Peroneal longus (PL) contribute greatly to ankle eversion; ankle eversion muscle strength will be measured using an isometric digital handheld dynamometer (MicroFET2, Manual Muscle Testing) under a standardized protocol [36, 37]. Participants will be placed in a prone position, and the ankle posture will be anatomically neutral. A handheld dynamometer will be placed on the lateral metatarsal head for the eversion testing. The patient will exert muscle strength, and the examiner will counteract with resistance for 5 s and measure the muscle strength isometrically. The healthy ankle will be examined first, followed by the injured ankle. The test will be performed thrice, with the highest value recorded in kilograms. The maximum strength (kg) will be taken as the participant’s peak strength and the result will be normalized by the body weight (kg). Both the injured and contralateral limbs will be tested.

##### Dorsiflexion range of motion

Weight-bearing lung test is based on the knee-to-wall principle and is a valid and reliable assessment that measures the DROM in CAI population. The procedure requires the participant to first perform a lunge in for the untested limb where the knee flexes to a point for the anterior knee to touch the wall with the tested heel remaining firmly on the floor. The maximum distance is determined from the tip of the great toe to the wall, nearest to 0.1 cm, using a long ruler [38]. Upon successful contact of the knee to the wall, the participant will progress backward in 1 cm increments from the wall until either the heel or the knee can no longer be maintained during the lunge. The participant will be given 3 attempts to achieve the greatest distance between the large toe and the wall. Both the injured and contralateral limb will be tested.

##### Lateral step-down test (LSDT)

LSDT is a clinical measurement that evaluates dynamic postural stability deficits and potential lower extremity injury. It measures the coordination of the lower limb joints, neuromuscular control, strength, pelvic stability, and range of motion [39]. A 30-cm high step will be used for the test, and the participant will be instructed to align the stance limb foot with the lateral edge of the step with their hands on their hips. Participants will also be instructed to descend the step with the tested heel gently touching the TekScan MatScan® pressure mat model 3150 (TekScan Inc, South Boston, USA), with the contralateral foot lifted off the platform. The trial will not be considered successful when the hands were not placed at the iliac crest during the starting point, the testing leg touches the pressure mat before the opposite leg left the step, or the participant jumped instead of stepping down. Participants are required to balance on the contralateral heel for 20 s, and the COP will be captured by the Sway Analysis Module (SAM™) software. Both the injured and contralateral limb will be tested; participants will repeat the test 3 times on each leg.

##### Cross-sectional and thickness of the peroneal muscle

Musculoskeletal ultrasound scanning will be performed in the supine position with the probe at 25% of the distance between the fibula head and lateral malleolus. Peroneus longus (PL) and peroneus brevis (PB) were scanned together transversely by positioning the long axis of the probe perpendicular to muscle fibers to obtain the image of the cross-sectional area (CSA) [40]. CSA will be taken as the area of muscle perpendicular to its longitudinal direction along the line between the fibular head and lateral malleoli. The probe will be rotated into a longitudinal orientation for the thickness of the peroneal longus (PL). The thickness will be defined as the distance between each peroneal muscle’s aponeuroses (white fibrous tissue) [40].

##### The elasticity of the peroneal muscle

In addition, the shear elastic modulus of a muscle will be measured using ultrasonic shear wave elastography (Aixplorer, Supersonic Imagine, France) with a linear array probe. The region of interest (ROI) will be set near the center of each muscle. The analysis area will be a 5-mm diameter circle at the center of ROI. The shear elastic modulus will be measured three times per muscle, and the average of the three measured values will be used for further analysis. The shear elastic moduli of the PL and PB will be measured at proximal 25% from the head of the fibula to the lateral malleolus. For each Q-box, the maximum, minimum, and mean (in kPa) of the stiffness of the muscle are measured [41].

Other patient-reported outcome measures (PROM) will be employed to assess overall health and foot and ankle-related symptoms, pain, physical activity level, and health-related quality of life. Foot and Ankle Ability Measure (FAAM) will be used to assess the foot and ankle functional limitations among CAI individuals. The FAAM consists of 29 items, scored between 0 and 4, divided into two subscales: activities of daily living (21 items) and sports (8 items) [42]. For score analysis, the percentage of each subscale is used separately. According to the International Ankle Consortium, values of the day living activities < 90% and < 80% of the sports subscales of the FAAM score were considered unsatisfactory. Manchester-Oxford foot and ankle questionnaire (MOXFQ) is a 16-question self-reported score designed to evaluate the impact of foot and ankle problems on a person’s quality of life. The dimensions comprise 3 subscales: walking/standing problem (7 items), foot pain (5 items), and issues related to social interaction (4 items). After that, all three domains of the MOXFQ can be summed up and converted to a metric from 0 to 100 to create a summary index score (MOFXQ index) [43]. The pain score will be evaluated using the visual analog scale (VAS) ranging from 0 to 100. For the pain score, the higher the score indicates, the more severe the pain. The Short Form-36 questionnaires (SF-36) will be used to evaluate the health-related quality of life [44]. The International Physical Activity Questionnaire will be used to evaluate the physical activity levels [45]. All primary and secondary outcomes will be evaluated at baseline, 4th week, 8th week, 3rd month, 6th month, and 12th month follow-up.

